### Demographic and health survey data

Demographic and Health Survey data sets are a household survey collected using a two-stage sampling method. Clusters for the sampling in Ghana used sampling frames of the 2000 and 2010 population and housing census to sample for the 2008 and 2014 DHS surveys respectively. For 2008, 412 clusters were determined in the first stage. In the second stage, 29 households were selected from each of the 412 clusters. Household from one cluster data was left out due to ethnic conflict at the time, thus 12, 323 households were selected.

The 2014 DHS also determined 427 clusters; 216 urban areas and 211 rural areas. The second stage then sampled 30 households per cluster for questionnaire administration in each household, thus, 12,831 households, similar to the sampling technique for the 2008 DHS.

In both situations, women between the ages of 15 and 49, who were either permanent residents in the selected households or stayed in the household the night before the selection were eligible to participate in the study and had their blood pressure measured. Sampling excluded women living in barracks, hotels, and prisons. Children between 0 and 59 months were also eligible and had their height and weight checked.

Eligible women participated in the study and answered questions on; age, pregnancy status, education, and relationship to the household head, residence, birth history, parity, pregnancy outcomes, knowledge and use of family planning methods, malaria interventions, diarrheal diseases, antenatal care and facility, and facility delivery (children born within the last 5 years).

Whereas GDHS 2008 collected data on the NHIS, the GDHS 2014 collected information on the free maternal health policy. Ghana and Kenya DHS surveys are similar in sampling procedures and methods and therefore comparable. DHS surveys are considered alternative to population and housing census in many situations due to their wide range of coverage in public health and socio-economic variables.

### Qualitative data setting

The second prong of the study employs a qualitative design to collect data from the Upper East Region (UER) of Ghana for analysis. The region is one of the poorest regions of Ghana [58, 66]. It is located in the north-eastern part of Ghana, bounded to Togo at the east, to Burkina Faso at the north, to the Sissala District at the west and the South by the West Mamprusi District.

The region is located between longitude 0° and 1° West and latitude 10° 30′ N and 11° N and has a total land area of about 8842 sq km with Bolgatanga as its capital. According to the 2010 population and housing census the population of the Upper East Region is estimated to be around 1,046,545 people, with 540,140 women, representing 51.6% of the total population [67].

The region has a national health insurance enrollment rate of 6.3% [68]. The majority of health care facilities in the region are publicly owned, with a good number of midwives comparatively. The Upper Region is a key player in the area of maternal healthcare utilization and has been a leader in the regional league since 2012 in the area of maternal healthcare.

According to the 2013 National Health Insurance Authority (NHIA) report, there are 211 accredited NHIS service providers in the region, many of which are clinics and health centers [51]. Ethnic groupings are sparsely distributed across the capital town; Bolgatanga at the center, Bawku area (to the east of the capital), and Navrongo area (to the west of the capital).

### Study population and sampling

Primary data will be collected from doctors, midwives, hospital administrators, and pregnant women in the Upper East Region. The region grouped into three zones; Central, Eastern, and Western Zones. One district hospital and two health centers each will be selected from the three zones using a simple random sampling technique, from where study participants will be recruited for the qualitative data collection.

Doctors from O&G departments in the hospitals, midwives from the labor ward and antenatal clinics in hospitals and health centers/CHPS compounds, and hospital administrators will be recruited purposively for one-on-one interviews. Even though hospital settings will be ideal to explore policy implementation bottlenecks, the inclusion of health centers will give rural perspectives to policy implementation from a typically developing country setting.

Pregnant women attending antenatal care (ANC) clinics in the selected facilities will also be recruited using convenient sampling methods after explaining the study rational to them at the antenatal clinic schools. The inclusion of pregnant women will add policy-user experience to the service provider perspective, epitome for the understanding of multiple realities as espoused by Creswell [69].

The Regional Director of Health Service for Upper East Region and the Director for Policy Planning Monitoring and Evaluation of the Ghana Health Service Headquarters will also be interviewed as Key Informants to provide top-level managerial context and viewpoints. Their inclusion will enhance data triangulation from multiple sources i.e. policy users, services provider perspective, and policy implementers viewpoint. The director's opinion will also serve to validate the results from the provider perspectives.

### Data collection

An open-ended interview guide will be used for the in-depth interviews (IDI), while fictional cases, developed for the purpose will guide the Focus Group Discussion (FGD). Interview sessions will be one-on-one and will last between 1 and 2 h per participant. Follow up questioning will be used to obtain clarity, where necessary.

The advantage of FGD is that it eliminates the fear of tagging and potential victimization among study participants while generating an in-depth understanding of participants' experience as Patton puts it "qualitative method permits inquiry into the selected issue in great depth with careful attention to detail, context, and nuance…”[70, 71].

The in-depth interviews and the group discussions will be audio tape-recorded and later transcribed verbatim for the analysis. The rationale for audio recording is to keep track of every comment shared by participants and this will be explained to participants to gain their consent. Table 3, below is a summary of the sample size, while Fig. 4 shows the clustered units of facilities, from where samples will be drawn.

**Table 3 Tab3:** Target participants

Method	Target	Size	Duration
KII	Director, PPME	1	1 h
KII	Regional director	1	1 h
IDI	Doctors	3	3 h
IDI	Midwives	12	6 h
IDI	Administrators	3	3 h
FGD	Pregnant women	30	3 h
Total		50	17 h

**Fig. 4 Fig4:**
[figure not shown]
Qualitative data collection tree showing source of primary data

### Inclusion criteria

Only staff (doctors, midwives, and administrators) of the selected hospitals, clinics, health centers, and CHPS compound with a minimum of three (3) years of working experience in the labor ward and antenatal clinic or facility will be interviewed. Also, only pregnant women of at least 18 years who access antenatal care or delivery services using national health insurance cards will be included in the focus group discussion.

### Exclusion criteria

Pregnant women whose health status is deemed unstable, using a parameter of vital signs; blood pressure, pulse, and respiration by the American Heart Association as shown in Table 4, will be excluded from the study. This is in line with the principle of non-malfeasance.

**Table 4 Tab4:** Vital signs criteria

Vital signs	Lower limit	Range	Upper limit
Blood pressure	90/60	90–130/60–85	130/85
Pulse	70	70–100	100
Respiration	16 cpm	16–22 cpm	22 cpm

### Statistical assumptions

The parallel trend assumption guide the use of DID analysis and assumes that no time-varying differences exist between the treatment and comparison groups of both countries. The second critical assumption for the difference in differences method is that the outcomes of interest in the two countries will move in tandem with or without the treatment. The Propensity Score Matching technique on the other hand assumes that, no systematic differences exist in the unobserved characteristics between the treatment group and the comparison group.

### Variables of interest

The maternal healthcare utilization examines two primary outcome variables which include; antenatal care up-take (4+ visit = 1, and ≤ 3 visits = 0), and facility delivery utilization, also binary outcome (facility delivery = 1 and home delivery = 0). Mothers’ health insurance status (proxy to the FMHCP) is the exposure variable of interest in this study.

Stillbirth, perinatal death, and neonatal mortality are secondary outcome variables of interest generated as binary outcomes from the DHS data sets using variable *b6,* and *b7* against which the policy utilization impact will be measured. Table 5 presents the derived variables generated using STATA 15.0 from the 2008/2014 DHS data sets.

**Table 5 Tab5:** Variables of interest

Item	Label	Name	Recoding	Binary V
1	Respondent holds valid NHIS card	*S1015*	Holds a valid NHIS card (with or with no evidence) = 1 No valid NHIS card = 0	*Vid_1*
2	Respondent hold valid NHIS card	*S1015*	Holds a valid NHIS card (with evidence) = 1 No valid NHIS card plus (holds a valid NHIS card with no evidence) = 0	*Vid_2*
3	Number of ANC visit during pregnancy	*m14*	Antenatal visits 0–3 = 0 Antenatal visits ≥ 4 = 1	*anc4*
4		*m15*	Home delivery = 0 All facility delivery = 1	*fdelivery*
5	Age at death	*b6*	Alive after day 0 = 0 Born dead/died on day 0 = 1	*stillbirth*
6	Age at death	*b6*	Did not die before 7th day = 0 Died before 7th day of life = 1	*prdeaths*
7	Age at death (months imputed)	*b7*	Did not die before 28th day = 0 Died before 28th day of life = 1	*neodeaths*

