Essentially, the ‘free’ policy lacked an operational framework for implementation, but had a political directive that ensured that every pregnant woman gets to register with the national health insurance scheme (NHIS), without paying a premium, and then access comprehensive maternal healthcare free of charge from NHIS accredited health service providers up to 90 days post-delivery [25, 27].

The government of Ghana has since invested several millions of Ghana cedis in a bid to keep the policy running amidst NHIS reimbursement challenges. With nearly 3million women benefitting from the ‘free’ package as by 2013 [28, 29], studies are yet to report on the policy gains or otherwise relative to perinatal healthcare outcome.

Despite the huge financial investment on the free policy intervention, literature is rather restricted to reporting on a nominal increase in attendance at healthcare facilities regardless of time-variant factors and somewhat monotonously on factors that affect the implementation process. Moreover, the existing literature turns to focus more on the policy effects on mothers and less on the unborn and the newborn.

Thus far, the ‘free’ maternal health care policy relationship with maternal healthcare utilization and outcomes, vis a vis medium to long term impact on perinatal healthcare has yet to be adequately documented [30–32].

Incidentally, perinatal death is also poorly researched in Ghana and Sub-Saharan Africa despite its economic burdening abilities [11, 14]. Stillbirth which accounts for a large portion of perinatal deaths has been estimated to have dire consequences on household healthcare expenditure, particularly in areas where the ratios are considered worse than child mortality due to malaria and HIV/AIDS [33–35].

This notwithstanding, perinatal deaths continue to receive little attention in public health and policy research [36, 37]. Hence, this current study seeks to examine the ‘free’ policy effect on maternal healthcare utilization after a decade of implementation and to measures its contributions towards the reduction of stillbirth, perinatal deaths, and neonatal mortality in Ghana.

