## The free maternal healthcare policy in Ghana

The FMHCP was introduced in Ghana through a political declaration in July 2008 by the government of Ghana, with no prior policy framework. Thus, the Ministry of Health (MOH) was tasked to ensure the successful implementation of the policy through the NHIS, an agency under the MOH. In principle, the MOH was tasked to enable the free registration of clinically confirmed pregnant women to access care from NHIS accredited facilities without paying out of pocket.

The policy had no sustainable funding source at the time but relied on an initial £42.5 million ($54.2 million) pledge from the UK government [53]. No clear cut eligibility criteria existed. One needed to be confirmed pregnant by a registered nurse, midwife, or doctor to be enrolled in the national health insurance scheme (NHIS) in the nearest office.

Between 2008 and 2014, the police had registered around 3 million women who benefited from comprehensive maternal healthcare in Ghana at no cost to them, but to the NHIS [28, 54]. With no premium payment, the NHIS appears short-circuited in terms of funding and perhaps, would have to rely on other sources, conventional or otherwise, to fund the ‘free’ policy.

Unsurprisingly, the insurance scheme has since reported funding deficit since the policy implementation characterized by erratic payment of service provider claims, which is copiously documented [47, 55–57]. The slow pace of reimbursement coupled with NHIS card issuance difficulties has created a situation of uncertainty surrounding the implementation of the ‘free’ policy [58].

It is in this light that, this study will seek to explore the current situation of the policy implementation by collecting in-depth primary data from the field of implementation i.e. hospital, clinic, and the policy users to situate the discussions of this study into proper context. Figure 2 presents the number of pregnant women beneficiaries of the policy, while Table 1, below show the proportional changes over the years, indicating inconsistencies in the trend.

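### NHIS card holding, not tied to the index birth, stands in for policy exposure in the card-based analyses, although nearly all 2008-round births predate the July 2008 launch

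*Protocol article*

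**What the plan says.** The Variables of interest section says that mothers' "health insurance status (proxy to the FMHCP) is the exposure variable of interest in this study". The Exposure variables section repeats this. Table 5 gives two codings of the same item, S1015, from the 2008 and 2014 surveys:

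- Vid_1: "Holds a valid NHIS card (with or with no evidence) = 1".
- Vid_2: "Holds a valid NHIS card (with evidence) = 1", with the reference category "No valid NHIS card plus (holds a valid NHIS card with no evidence) = 0".

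The article's own facts about timing are:

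- Births: the survey questions cover "facility delivery (children born within the last 5 years" before interview.
- Launch: the policy was "introduced in Ghana through a political declaration in July 2008" (The free maternal healthcare policy in Ghana).
- Entitlement: registered women receive free care from "NHIS accredited health service providers up to 90 days post-delivery" (Background).
- Data content: the 2008 survey collected insurance data, whereas "the GDHS 2014 collected information on the free maternal health policy" (Demographic and health survey data). Table 5 lists no variable for that policy information.

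The Study design section treats the 2008 surveys as baseline. The Data analysis section merges the two Ghana files to n = 8,876 for matching.

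**The concern.** An exposure variable should describe the woman's status during the pregnancy and delivery whose outcome is analysed. S1015 is worded in the present tense, and the article gives it no other timing, so it has to be read as status at interview. Two problems follow.

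1. In the 2008 round, a birth before July 2008 cannot have been exposed to the policy. If the mother holds a card, the proxy still takes the value 1.
2. In the 2014 round, a child may be up to five years old at interview. A card may have been obtained, renewed or lost since that birth.

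Objective 1, the first null hypothesis (antenatal uptake and the policy) and the tests and regressions on the two primary outcomes rest on this variable. If it mixes policy registration with ordinary membership and with later card holding, its coefficient cannot be read as a policy effect. The Scope and limitations section does not mention the proxy.

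**Working it through.** **Inputs from the article.** Ghana records 2,992 (2008) and 5,884 (2014); birth window 5 years (60 months); launch July 2008; free care up to 90 days after delivery.

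**Assumptions, not in the article.** Births evenly spread over the window; 2008 interviews completed by the end of December 2008; card prevalence as stated in step 3.

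**1. The plan's figure.** 2,992 + 5,884 = 8,876, as stated. The 2008 share is 2,992/8,876 = 33.7%.

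**2. Births that predate the policy.** At most 6 of the 60 months in the 2008 window follow launch.

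- Pre-launch share: at least 1 − 6/60 = 90%.
- Pre-launch births: at least 0.90 × 2,992 ≈ 2,693, which is 2,693/8,876 = 30.3% of the merged file.
- Post-launch births sitting in the baseline: at most 0.10 × 2,992 ≈ 299.

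With 2014 interviews, a five-year window reaches back no further than 2009, so all 2014-round births follow launch.

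**3. Share of card-coded births that predate launch, if the merged file is analysed by card.** With card prevalence c08 and c14 and pre-launch share s, the share is 2,992·s·c08 / (2,992·c08 + 5,884·c14). I vary c08 over 0.3–0.4 and c14 over 0.4–0.7.

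- Lowest (c08 0.3, c14 0.7, s 0.9): 807.8/(897.6 + 4,118.8) = 16%.
- Middle (c08 0.4, c14 0.6, s 0.9): 1,077.1/(1,196.8 + 3,530.4) = 23%.
- Highest (c08 0.4, c14 0.4, s 1.0): 1,196.8/(1,196.8 + 2,353.6) = 34%.

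**4. Time between birth and interview.** 90/(5 × 365.25) = 4.9% of births fall within 90 days of interview. For about 95%, free care for that birth had ended by then. This measures timing and is not an error rate.

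**5. Illustration of attenuation.** If misclassification does not depend on the outcome, the observed risk difference is the true one times PPV + NPV − 1, which depends on true exposure prevalence. The sensitivity and specificity pairs are illustrative.

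| Sensitivity / specificity | True exposure | PPV | NPV | Factor | A true 10 points becomes |
|---|---|---|---|---|---|
| 0.9 / 0.9 | 40% | 0.86 | 0.93 | 0.79 | 7.9 |
| 0.7 / 0.8 | 40% | 0.70 | 0.80 | 0.50 | 5.0 |
| 0.7 / 0.8 | 60% | 0.84 | 0.64 | 0.48 | 4.8 |
| 0.8 / 0.7 | 20% | 0.40 | 0.93 | 0.33 | 3.3 |
| 0.5 / 0.6 | 40% | 0.45 | 0.64 | 0.10 | 1.0 |

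The shortcut sensitivity + specificity − 1 would give 0.50 in the fourth row, so it should not be used away from 50% prevalence.

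**6. Which analyses use the card.**

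- *Tests and regressions on antenatal uptake and facility delivery* (Data analysis): yes, insurance status is the independent variable.
- *Difference-in-differences* (Table 2 and Data analysis): no, it contrasts country by survey year.
- *Matching as described in Study design*: no, treated means the 2014 survey and untreated the 2008 survey.
- *Matching under the Operational definitions*: the antenatal branch requires insurance registration in both groups and separates them by number of visits. The facility-delivery branch names no insurance condition.
- *Matching on the exposure in Variables of interest*: yes, fully.

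The article therefore gives several incompatible meanings of treatment.

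**The case against.** The strongest defence is that the estimators named for policy impact need not use the card. Difference-in-differences compares country and year, and matching by survey round makes every 2008 woman untreated whatever card she holds. This stands and limits the point to the card-based analyses. It is not a full answer, because the Operational definitions and Variables of interest sections define treatment or exposure through insurance and the article does not say which definition governs the matching.

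A second defence is that the policy works through insurance registration, so insurance status is the natural route of exposure, and the article openly calls it a proxy. That is fair for births after launch. It cannot hold for births before it.

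Several stronger readings are tempting but not supported:

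- *About 95% of births are misclassified.* The 90 days limit free care. The article does not say when a card expires, so a card held later may be the one issued in pregnancy.
- *The 2014 survey holds a ready birth-level policy measure.* The article says only that policy information was collected. It does not show that the item refers to the index birth or was asked of all women.
- *The bias must run towards the null.* That requires error unrelated to outcome. Women who keep or renew a card may differ in care seeking; wealth index is a planned adjustment variable, but this covers only part of that difference.
- *Vid_2 is a coding error.* Vid_1 already gives the broad definition, so the stricter one is a reasonable variant. Neither addresses timing.

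**Conclusion.** The point holds for the card-based association tests and regressions on the primary outcomes, and for any matching whose treatment is defined through insurance. As written, S1015 codes policy exposure for 2008-round births that could not have had it: at least about 90% of 2,992 predate launch, given evenly spread births and fieldwork ending by December 2008. If the merged file is analysed by card, some 16% to 34% of births coded exposed would predate the policy under the assumed card prevalences. For 2014 births the card is not tied to the pregnancy, and the extent of error is unknown.

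The direction and size of the resulting bias cannot be fixed from the article, and the attenuation table is illustrative only. A reader might infer that every policy estimate in the study is compromised. The documents do not support that, because difference-in-differences by country and year and matching by survey round do not use the card.

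**What to change.** 1. State one definition of treatment for each analysis, and reconcile the Operational definitions, Study design and Variables of interest sections.
2. Do not treat card status as policy exposure for births before July 2008. Restrict the card-based policy analysis to births after launch, in effect the 2014 round. Use the 2008 births only as the pre-policy period, or as a placebo check of how card holding relates to the outcomes without the policy. Remove post-launch births (at most about 299) from the baseline.
3. Use the policy information collected in 2014 as the 2014 exposure if it can be linked to the index birth, with the card as a sensitivity analysis.
4. Add a card analysis limited to the most recent births, for example the last 12 months. This narrows the timing gap but does not close it: 90/365.25 = 25% of those births fall within 90 days of interview.
5. List the proxy as a limitation. Show any attenuation as an illustration, using PPV + NPV − 1.

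The work is recoding of data the plan already uses. The cost is precision. Moving from 8,876 to at most 5,884 records widens standard errors by about √(8,876/5,884) = 1.23, other things equal. The 12-month analysis keeps about one fifth of births (5,884/5 ≈ 1,177), a further factor of about √5 = 2.2. Any contrast that codes pre-launch births as unexposed also ties exposure to calendar time, so secular change would be confounded with the policy and this must be stated.

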### Exposure variables

The National Health Insurance status [proxy to the ‘free’ maternal healthcare policy (FMHCP)] is the main exposure variable. However, on the secondary level of analysis, antenatal care up-take (binary) and facility delivery utilization (also binary) are independent predictors, through which the secondary outcomes of interest; stillbirth, perinatal death, and neonatal death can be measured.

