## Conceptualization

Literature has shown that drivers of maternal and child healthcare include characteristics such as; maternal age, gestational age, parity, educational level, wealth index or income, multiple pregnancies, and area of residence [10, 38–40]. These factors are thought to significantly influence the uptake of antenatal care and skilled delivery [41–43]. The overall effect of the factors are moderating and have direct or indirect links to undesirable perinatal outcomes.

Institutional level factors also exist, often at the point of service delivery, and tacitly restrict the full realization of healthcare objectives. They impede policy implementation and influence outcomes of health policy interventions. For example, factors such as staff competence, health facility location, and quality of care are critical to the attainment of the primary outcomes of interest and also play roles to influence the undesirable outcomes.

This study attempts to draw lessons from the Street-Level Bureaucratic theory, as propounded by Lipsky, to examine how service providers, the lower level employee negotiate with policy users to partner government in the implementation of the FMHCP for optimum effect.

Lipsky opined that in policy implementation, the lower level employee is faced with challenges and exercises discretions. He maintained that the employee is the last link to policy formulation and should not be left out in developing workable policies [44, 45] and that, the lower-level employee which he termed the Street-Level Bureaucrat, is the one with the actual implementation role of public policy [48, 46].

The ‘free’ maternal health care policy in practice exercises causal effects through policy effectiveness, and therefore undesirable effects if challenges are present. Thus, this current study proposes a framework (Fig. 1) of quantitative and qualitative design to examine the FMHCP quantum contribution towards maternal healthcare utilization and its effects in combating perinatal deaths.

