## Operational definitions

*Utilization*: The use of maternal healthcare services rendered in a healthcare facility at any level.

*Maternal healthcare*: Antenatal care clinics and facility delivery services provided to pregnant women in a healthcare facility.

*Antenatal care uptake*: This refers to a 4+ antenatal care visit, thus, antenatal clinic visits of less than 4 are equal to zero visits (or 'no visit').

*Facility delivery*: This is when a pregnant woman gives birth in a healthcare facility at any level.

*Stillbirth*: This refers to the birth of a fetus with no signs of life, after 28 weeks of gestation or the death of a fetus within 24 h after birth.

*Perinatal death*: This refers to the number of stillbirth plus the death of neonates within the first week of life.

*Neonatal deaths*: This refers to the number of newborn deaths within 28 days of life.

*Treatment group*: Pregnant women study participants registered with the national health insurance scheme and made 4+ antenatal care visits or pregnant women participants in Ghana who delivered in a healthcare facility.

*Comparison group*: Pregnant women study participants registered with the national health insurance but have made less than 4 antenatal care visits with less than four minimum antenatal visits or pregnant women who did not deliver in a healthcare facility within the study period.

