### Covariates

Covariates are the moderating factors identified in the study conceptual framework. Covariates that show significant association with the variables of interest under consideration will be controlled for using multiple logistic regression. These include maternal characteristics such as; age, parity, pregnancy status, cesarean section, educational status, twin pregnancy, income level, abortion, and marital status. These will be adjusted for as confounding using logistics regression models. Population characteristics such as wealth index, distance, region, educational status, and rural/urban residence will also be adjusted for as confounding variables [42].

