### Data analysis

The secondary data will be cleaned and organized, dropping irrelevant variables and renaming covariates for ease of reference as necessary. Essentially, variables of interest in this study are binary outcomes i.e. 1 = case/the presents of an intervention, and 0 = no case, the absence of intervention, control.

Both multivariate logistic regression and Poisson with robust standard error, or negative binomial regression depending on whether there is over dispersion (conditional variance exceeding the conditional mean) will be fitted and analyzed. Thus, **loge** {*p*1 / *(1—pi)*} = *b0* + *b1 Xi1* + *b2 Xi2* + … + *bkXik*. The Use of the multiple logistic regression model also comes with the advantage of adjusting for confounding by including the covariates in the model.

For the matching method, Ghana’s DHS data sets (2008 and 2014) will be merged. This will increase the sample size to n = 8876, and add power to the study. The merger will also eliminate the risk of lack of common support, the so-called curse of dimensionality, a common phenomenon in propensity score matching, where treated units propensity scores cannot find suitable pairs.

Descriptive data will be presented using tables, frequencies, and proportions. The data will then be analyzed distinctly, using multiple statistical models and quasi-experimental design techniques. Firstly, the student independent *t*-test will be used to test for proportions, the significance of association, and mean differences between the independent variable, and the binary outcomes of interest; antenatal care uptake, and facility delivery utilization.

Test of association set < 0.05 less of significance, between the secondary variables of interest (stillbirth, perinatal death, and neonatal mortality) and the covariates; mothers age, marital status, level of education, wealth index, region, area of residence, twin delivery, parity, and employment status will be determined by using the Rao Scot Chis-square, which has an added sensitivity advantage, while adjusting for complex survey design features (weighting, clustering and stratification).

Only covariates found to be significantly associated with the dependent or independent variables will then be included in a multiple logistic regression model and adjusted for confounding [72].

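### Using the completed count of 4+ antenatal visits as a predictor of stillbirth, perinatal and neonatal death builds in a bias towards apparent protection, because early delivery cuts the count short

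*Protocol article*

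**What the plan says.** - **Role.** Exposure variables makes antenatal uptake a predictor of stillbirth, perinatal death and neonatal death in the second tier of the analysis. Its wording is "antenatal care up-take (binary) and facility delivery utilization (also binary) are independent predictors, through which the secondary outcomes of interest".
- **Definition.** Table 5 (Variables of interest) derives the variable from m14, "Number of ANC visit during pregnancy", cut at 4. Operational definitions adds that "antenatal clinic visits of less than 4 are equal to zero visits". The count is not tied to any gestational week.
- **Treatment group.** Operational definitions counts as treated the women "registered with the national health insurance scheme and made 4+ antenatal care visits", or those in Ghana who delivered in a facility. The comparison group mirrors this with fewer than 4 visits, or no facility delivery.
- **Outcome window.** Stillbirth is a birth without signs of life "after 28 weeks of gestation or the death of a fetus within 24 h after birth".
- **Gestational age.** Conceptualization lists the drivers of care as "maternal age, gestational age, parity, educational level, wealth index or income, multiple pregnancies, and area of residence", and ties them to antenatal uptake and to undesirable perinatal outcomes. The covariates to be tested against the death outcomes (Data analysis) are "mothers age, marital status, level of education, wealth index, region, area of residence, twin delivery, parity, and employment status". The maternal list under Covariates is "age, parity, pregnancy status, cesarean section, educational status, twin pregnancy, income level, abortion, and marital status". Gestational age is in neither list.

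**The concern.** The exposure is known only when the pregnancy is over. A woman who delivers at 30 weeks has had fewer weeks in which to make a fourth visit than one who delivers at 40, and her baby is more likely to die. Short gestation therefore pushes the exposure towards 0 and the outcome towards 1 at the same time. Because 1 to 3 visits are scored as none, a woman who was attending on schedule until an early delivery is grouped with women who never attended.

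This differs from ordinary confounding by wealth or education, which the plan does address. It comes from how the exposure is counted, and its own direction is known: towards benefit. Expected outcome already anticipates favourable associations with the death outcomes, so a spurious protective estimate would match expectation and be hard to notice.

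**Working it through.** **The plan's own figures.** The protocol gives no effect size or bias figure for this analysis. The one related figure is the merged Ghana sample: 2992 + 5884 = 8876, which reproduces.

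**Inputs.**
- From the protocol: overall death risk 0.030 (the 30 neonatal deaths per 1000 for Ghana 2008, under Kenya as a comparison country); n = 8876; significance at 0.05, two-sided assumed.
- Assumed: preterm share q; preterm-to-term ratio of death risk k; probability of 4+ visits a at term and b in preterm births.

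**Two-stratum model in which antenatal care has no effect on death.**
- Term risk r0 = 0.030 / (1 − q + qk); preterm risk r1 = k·r0.
- Share with 4+ visits: P4 = (1 − q)a + qb.
- Risk with 4+ visits: d4 = [(1 − q)a·r0 + q·b·r1] / P4.
- Risk with fewer than 4: d3 = [(1 − q)(1 − a)r0 + q(1 − b)r1] / (1 − P4).
- Spurious risk ratio = d4 / d3.

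**Mid case: q = 0.10, k = 6, a = 0.80, b = 0.60.**
- r0 = 0.030 / (0.90 + 0.60) = 0.020; r1 = 0.120.
- P4 = 0.72 + 0.06 = 0.78.
- d4 = (0.72 × 0.020 + 0.06 × 0.120) / 0.78 = 0.0216 / 0.78 = 0.0277.
- d3 = (0.18 × 0.020 + 0.04 × 0.120) / 0.22 = 0.0084 / 0.22 = 0.0382.
- Risk ratio = 0.73 with no true effect. With all 8876 records in the comparison, the chance of p < 0.05 is about 66%, before any design effect.

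**Ranges, with a = 0.80.**

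| Preterm share q | Risk ratio k | Preterm women reaching 4+ (b) | Spurious risk ratio |
|---|---|---|---|
| 8–12% | 5–10 | 70% | 0.78–0.88 |
| 8–12% | 5–10 | 60% | 0.63–0.78 |
| 8–12% | 5–10 | 50% | 0.52–0.70 |
| 5–15% | 3–10 | 40–70% | 0.42–0.95 |
| any | any | 80% (as at term) | 1.00 |

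The last row is the control: with no shortfall in visits among preterm births there is no bias.

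**Simulation (2,000,000 pregnancies, no antenatal effect, overall risk 0.030).** Assumed: 10% preterm, spread over 28 to 37 weeks; first visit around week 18 (SD 6); visits every 4 or 6 weeks until delivery.

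| Risk by gestation | 4-weekly visits | 6-weekly visits |
|---|---|---|
| Graded: 8-fold before 32 weeks, 3-fold at 32–36 | 0.43 | 0.58 |
| Mild: 2-fold before 37 weeks | 0.79 | 0.87 |
| No link with gestation | 1.01 | 1.00 |

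In the same simulations, restricting to term births gave 1.00 to 1.03. Counting the visits that would have accrued by 40 weeks also gave 1.00 to 1.03. Removing the truncation removes the effect, so truncation is its cause here.

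**The case against.** **Reach.** A reader might infer that the whole perinatal half of the study is compromised. The documents do not support that. For deaths, Objective 3, Research questions 2 and 3, and the second and third hypotheses all name facility delivery as the exposure. The Ghana–Kenya difference-in-differences compares countries over time, not women by visit count. The matching described under Study design compares 2014 with 2008. What stands is the explicit commitment under Exposure variables and the 4+ branch of the treatment definition.

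**Covariates.** A reader might infer that gestational age is definitely excluded. Covariates opens by tying the adjustment factors to the conceptual framework, where gestational age appears, and its list is illustrative. The list in Data analysis is specific to the death outcomes and omits it. The text is therefore ambiguous rather than settled; Figures 1 and 3 were not available for this check. Pregnancy status is not gestation at delivery, and adjusting for twins and cesarean section would capture only part of early delivery.

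**Certainty.** A reader might infer that antenatal care is bound to look protective. That is true of this component, not of the net estimate. Women at high risk may attend more often, which acts the other way; Background itself describes screening to select them for monitoring. The risk ratios above are crude, whereas the plan adjusts. It would also be wrong to say that most deaths fall in very early births. No section says so, and in the model all preterm births together carry qk / (1 − q + qk) of deaths, which is 30% (q = 0.08, k = 5) to 58% (q = 0.12, k = 10).

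**Remedy.** Adjusting for gestation, or restricting to term, conditions on something antenatal care may itself change. This objection stands and limits how those analyses can be used.

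**Conclusion.** The point holds in limited form. The completed 4+ count should not serve as a causal predictor, or as a treatment definition, for the death outcomes, because truncation by early delivery adds a bias towards apparent protection. Neither the specific covariate list nor the matching assumption of no systematic unobserved differences (Statistical assumptions) deals with it, and Scope and limitations does not mention it.

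Its size is not fixed by the documents. Under the main assumptions the spurious crude risk ratio is about 0.5 to 0.9. The wider grid runs from 0.42 to 0.95. It depends chiefly on how far short of 4 visits preterm pregnancies fall, for which the protocol gives no figure. Confidence is high in the mechanism and in its own direction. It is not high in the net direction or the statistical significance of the final estimate.

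The scope is the antenatal-to-death secondary analysis and any death comparison that uses the 4+ treatment branch.

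**What to change.** 1. Keep 4+ visits as a primary utilization outcome. Under Exposure variables and Operational definitions, stop using it as a causal predictor or treatment criterion for stillbirth, perinatal death and neonatal death.
2. For deaths, use an antenatal measure fixed early in pregnancy, such as first visit in the first trimester, if the data sets hold it. State that it measures timing rather than number of visits.
3. If pregnancy duration is available, add a term-only analysis as a sensitivity analysis only, stating that it may remove any benefit that acts through preventing early delivery.
4. If neither variable is available, report the 4+ association with death as descriptive and state that truncation biases it towards benefit.
5. Reconcile Conceptualization, Covariates and Data analysis on whether gestational age is a covariate.

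**Cost.** Protocol wording and one recode of existing survey data, with no new data collection. The price is a changed question (timing instead of number of visits) or, under step 4, giving up a causal claim for the antenatal component. The protocol's description of the data names neither replacement variable, so step 4 may be all that is achievable.
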